### Third phase: Training content design

3.7

The content of the training intervention will be developed based on the common factors of FOC among Iranian nulliparous women from the first and second phases of the study.

### Fourth phase: Randomized controlled trial

3.8

The fourth phase of this study will be performed, and its results will be reported based on the CONSORT (Consolidated Standards of Reporting Trials) 2010 checklist (Schulz et al., 2011).

#### Study design, participants and setting

3.8.1

In this educational trail RCT, the statistical population consists of all nulliparous women visiting comprehensive health service centres of Bostanabad.

The inclusion criteria are being nulliparous, being at gestational age 6 to 12 weeks (The first trimester of pregnancy is selected to better manage the FOC from the beginning of pregnancy and follow‐up to maintain the intervention for 6 months during pregnancy), being 18–35 years old, having a high school diploma or higher educational degree, no history of depression or long‐term medical illness in the past, singleton pregnancy, ultrasound confirmation of foetal health, no history of miscarriage or stillbirth, no contraindications for vaginal delivery during the study until the end of pregnancy, not being graduated in midwifery or relevant majors and willingness to participate in the study. The exclusion criteria are also emergencies requiring preterm delivery, indications for caesarean section, a history of caesarean section, a history of infertility, irregular attendance in training sessions, refusal to complete the questionnaire and no access to the participant for any unpredictable reason.

#### Sampling method

3.8.2

First of all, a list of nulliparous women who met the inclusion criteria will be extracted from all health centres of Bostanabad. The sample size for each centre will be determined, and then some women will be randomly selected from each centre. The selected women will be contacted through their contact information to be briefed on the research objective and procedure and then be invited to participate in the study. Sampling will continue until the predetermined number of participants enters the study.

#### Randomization

3.8.3

The participants will be assigned to two parallel groups of control and intervention using blocked randomization with blocks of 4 and 6. For allocation concealment, the names “Control” and “Intervention” will be written on two separate pieces of paper by a person who will have no role in sampling and data analysis. The pieces of paper will be put inside numbered identical opaque envelopes. Each participant will be given one of the envelopes by the health staff in each centre to be assigned to one of the groups. All participants who will take the measurements will be blinded to the assigned study groups. In the final phase of the study, the intervention will be performed by the researcher.

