The research team will try to finish all the training sessions before the 16th week of pregnancy and conduct the posttest in two phases (the first one immediately after the intervention and the second one during the third trimester of pregnancy [6 months after the intervention]). The participants will be asked to complete the questionnaires once again in the posttest and explain the delivery method and the reason for choosing it after childbirth. Until the end of the study, we will be in touch with the participants to the retention and follow‐up completely in the WhatsApp group.

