#### Data collection

3.8.5

The measurement tools of this study are a demographics questionnaire, the Wijma Delivery Expectancy/Experience Questionnaire (W‐DEQ), Antonovsky's sense of coherence scale (SOC), and a choice of delivery method checklist. All these tools will be completed by participants themselves (self‐reporting). It is noteworthy that there would be changes in the measurement tools depending on the component obtained from the first and second phases of the study.

The W‐DEQ was developed by the Sweden Klaas Wijma in 1998 (Wijma, Wijma, & Zar, 1998). The W‐DEQ is a short, practical and common tool for evaluating FOC (Badaoui et al., 2019). This tool consists of 33 items that are scored based on a 6‐point Likert scale (from 0: very much to 5: not at all). The total score on this scale ranges between 0 and 165, and higher scores indicate higher levels of FOC. As the cut‐off point of this scale is 85, scores over 85, under 38, between 38 and 65 and between 66 and 84 represent clinical fear, mild fear, moderate fear and severe fear, respectively.

The 13‐item Antonovsky's sense of coherence scale (SOC‐13) measures comprehensibility (5 items), manageability (4 items) and meaningfulness (4 items) (Antonovsky, 1993). The items are scored based on a 7‐point Likert scale and the total score on this scale ranges between 13 and 91. A score within the ranges 13–60, 61–75 and 76–91 indicates low, moderate and high levels of SOC, respectively (Voogand et al., 2020).

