## Appendix A

### A.1 DATA SET CATEGORY

**Table jats-table-wrap-1:**

Data set category	Information
Primary registry and trial identifying number	irct.ir IRCT20210506051202N1
Date of registration in primary registry	21 Aug, 2021
Secondary identifying numbers	–
Source(s) of monetary or material support	Tarbiat Modares University
Primary sponsor	Tarbiat Modares University
Secondary sponsor(s)	–
Contact for public queries	[name], Ph.D Student of Health Education and Health Promotion [[name]] [[contact]]
Contact for scientific queries	[name], Ph.D Student of Health Education and Health Promotion [[name]] [[contact]]
Public title	Saltuogenesis theory on fear of childbirth
Scientific title	Design, implementation, and evaluation of educational program based on saltuogenesis theory on fear of childbirth and choice of delivery method among nulliparous women: a sequential‐exploratory mixed methods design
Countries of recruitment	Iran
Health condition(s) or problem(s) studied	Fear of childbirth
Intervention	Educational content is prepared based on the main factors obtained from qualitative and review stages on the fear of childbirth in nulliparous women. The educational intervention is held in 4 training sessions of at least 30 min in 4 groups of 6 people and 2 groups of 7 people, one day a week for each group at the Health Comprehensive Service Centers of Bostanabad city of East Azerbaijan by the researcher in face to face. All of the training sessions will be completed by the 16th‐week gestation.
Key inclusion and exclusion criteria	Inclusion criteria: 18–35 years, High school and university, no history of self‐reported depression or long‐term illness, singleton pregnancy, ultrasound confirmation of foetal health, no history of miscarriage or stillbirth, lack of contraindications of vaginal delivery to termination of pregnancy, lack of midwifery base and related fields of study, having consent to participate in the study. Exclusion criteria: preterm delivery due to an emergency, indications for caesarean section, history of caesarean section, history of infertility, lack of continuous presence of pregnant women in training sessions, failure to complete the questionnaire, lack of access to the participant for any unpredictable reason.
Study type	Interventional Allocation: randomized Intervention model: parallel assignment Masking: Single blinded (assigned study groups.) Primary purpose: Education/Guidance
Date of first enrolment	Expectant

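### The plan claims that the participants who take the measurements are blinded and labels the trial single-blind, but the design cannot blind women who self-report every outcome

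*Protocol article*

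**What the plan says.** Section 3.8.3 (Randomization) of the protocol article states: "All participants who will take the measurements will be blinded to the assigned study groups". The registry data set in Appendix A.1 gives "Masking: Single blinded (assigned study groups" and does not say which party is masked.

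The surrounding sections describe the following:

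- **Before enrolment** (3.8.2, Sampling method): selected women are "briefed on the research objective and procedure and then be invited to participate in the study".
- **Allocation** (3.8.3): "the names “Control” and “Intervention” will be written on two separate pieces of paper". These are placed inside numbered, identical, opaque envelopes. Then: "Each participant will be given one of the envelopes by the health staff in each centre to be assigned to one of the groups".
- **Treatment contrast** (3.8.4, Intervention): controls get the routine training of the health centres. The intervention arm gets the same plus weekly in-person group sessions, with text reminders. No sham or attention control is described.
- **Provider** (3.8.3 and 3.8.4): the researcher delivers the intervention, and a doctoral student in health education leads the sessions.
- **Measurement** (3.8.5, Data collection): "All these tools will be completed by participants themselves". This covers the W-DEQ, the SOC-13 and the delivery-method checklist. After birth, women are also asked to "explain the delivery method and the reason for choosing it after childbirth" (3.8.4).
- **Primary outcomes** (3.8.7): reduced fear of childbirth and selection of vaginal delivery.

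**The concern.** The plan claims a property that the design lacks. A woman who has been told how the study works, and who then does or does not attend weekly classes, knows her arm. She is also the only person who records her outcomes.

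This matters because the intervention aims to lower fear and to encourage vaginal delivery, and the first post-test comes immediately after the sessions. Women who have just finished such a course have a reason to report less fear and a preference for vaginal delivery, whatever they privately feel. Controls have no matching reason. Absence of blinding is inherent in adding classes to routine care and is not in itself a fault. The fault is that the plan states the opposite, so that readers and systematic reviewers would rate the risk of bias in both self-reported primary outcomes too low. Section 4.1 (Limitation) does not mention it.

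**Working it through.** The point rests on the text, so the first step is to ask of each party whether the document supports blinding.

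| Party | What the document describes | Can be called blinded? |
|---|---|---|
| Participants | Briefed on the procedure; classes in one arm only; no sham | No |
| Session leader | The researcher, who delivers the intervention | No |
| Outcome assessor | None apart from the participant; all tools self-completed | No such person described |
| Person preparing the papers | Kept out of sampling and data analysis | This protects concealment, not blinding |
| Data analyst | Anonymous analysis is promised in 3.8.10, as a matter of confidentiality | Masking to arm is stated nowhere |

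Nobody is identified who would make the single-blind label true.

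**Alternative reading of the sentence.** The English is awkward and may have been meant for those who administer the measurements. Section 3.8.5 closes that route: the women complete all the tools themselves, so the people who take the measurements are the participants.

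**Which outcomes are exposed.** W-DEQ fear and stated choice of delivery method are subjective and self-reported, so they are the most exposed. SOC, the secondary outcome, is exposed in the same way. Whether a woman had a caesarean is a salient fact and leaves little room for misreporting.

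**Illustration of scale (the shift is an assumption).** The only input from the plan is 38 per group (3.8.8). The plan's formula reproduces it: (1.960 + 0.842)² × (4.8² + 3.7²) / 3² = 7.849 × 36.73 / 9 = 32.03, and 32.03 × 1.20 = 38.4, stated as 38. The documents give no reporting shift, so a range is used. Suppose there is no true effect and the arms differ by a reporting shift of b SD on a continuous score. The false-positive probability of a two-sided 5% comparison of means is then

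Φ(b/SE − 1.96) + Φ(−b/SE − 1.96), with SE = √(2/n).

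For n = 38, SE = √(2/38) = 0.229. For b = 0.2, b/SE = 0.872, giving Φ(−1.088) + Φ(−2.832) = 0.138 + 0.002 = 0.141. If 20% are lost, 38 × 0.8 = 30.4, so n = 30 is shown as well.

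| Assumed shift b (SD) | n = 38 per group | n = 30 per group |
|---|---|---|
| 0.1 | 7.2% | 6.7% |
| 0.2 | 14.1% | 12.1% |
| 0.3 | 25.8% | 21.3% |
| 0.5 | 58.7% | 49.1% |

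These figures show what a shift of a given size would do. They do not show that any such shift will occur.

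**The case against.** The strongest reply is that most of this is unavoidable. Fear on the W-DEQ is self-reported by nature, and classes added to routine care cannot be masked. That is true, and it confines the correctable defect mainly to what the plan claims about itself.

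A reader might also infer more than the documents support:

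- **That the envelopes reveal the arm.** They are identical and opaque with the paper inside, and the text does not say who opens them. Knowledge of allocation follows from the briefing and from attending, or not attending, the sessions. The point does not need the envelope.
- **That the registry entry is plainly false.** It does not say who is masked. It is unsupported and unclear, whereas the sentence in 3.8.3 is wrong as written.
- **That reported delivery mode is seriously biased.** A woman's account of how she gave birth is little prone to misreporting, and 3.8.4 does not say who collects it.
- **That records should replace the choice outcome.** Choice of natural childbirth is a registered primary outcome, and 3.3 lists choice and post-delivery choice as separate objectives. Correcting a masking statement is no ground for replacing it. Nor does the document say that the health centres hold mode of birth: household records appear only as the source for selecting interviewees (3.5.1).
- **That the bias can be scaled against the planning effect in 3.8.8.** Those means belong to the meaningfulness component of SOC, which is the secondary outcome. They say nothing about the size of effect on fear or delivery choice.

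**Conclusion.** The concern holds in this limited form. The claim of participant blinding in 3.8.3 is wrong as written, and the single-blind label in Appendix A.1 is unsupported because no blinded party is identified. The self-reported outcomes, chiefly W-DEQ fear and stated choice of delivery method, must be read as unblinded.

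The conclusion rests only on the article's own account of the briefing, the difference between the arms and self-completion. It would change for the masking field, though not for the participants, if the sponsor named a party who is in fact blinded. The size of any reporting bias cannot be derived from the documents, and the false-positive figures are conditional on assumed shifts. The point does not call the randomisation or the allocation concealment into question. The correction is worth making because it is cheap and changes how both primary outcomes should be interpreted.

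**What to change.** 1. In 3.8.3, delete the sentence claiming participant blinding and state that participants and the session leader are not blinded.
2. In Appendix A.1 and the registry, correct the masking field so that it names who is blinded, if anyone. The data analyst may be named only if masking to arm will really be carried out.
3. In 4.1, list unblinded self-report as a limitation, and interpret the W-DEQ and stated-choice results accordingly.
4. Have completed questionnaires returned by a route that does not pass through the session leader.
5. Where records are accessible, confirm actual mode of birth from them for the post-delivery objective in 3.3. Keep the registered choice outcome as it is, labelled as self-report.

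Items 1 to 3 cost a text edit and a registry update, and the trial will report its masking less favourably. Item 4 needs a small change in logistics. Item 5 needs a look-up for at most 76 women and depends on record access, which the document does not establish. Appendix A.1 lists the start of recruitment as expected, so on the article's own timeline all of this can precede enrolment.

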#### Intervention

3.8.4

Based on successful evidence in this area (Bonmatí‐Tomas et al., 2019; Heggdal, 2015; Heggdal & Lovaas, 2018; Odajima et al., 2017; Tan et al., 2014, 2016), the training intervention will be performed in four sessions of at least 30 min by using appropriate audio‐visual training methods and tools to investigate each of the common factors of FOC obtained from the qualitative and review phases of this study. It is noteworthy that there would be changes in the number and duration of sessions based on the content obtained from the first and second phases of the study. Training sessions will be held in person probably in four groups of six and two groups of seven. However, the size of the groups may be determined depending on the conditions of the study group, the location of sessions and the number of samples selected from each centre. If the COVID‐19 pandemic reaches a stable state, the training sessions will be held under appropriate physical distancing and health protocols.

For the ease of group management and convenience of participants, training sessions will be held once a week for each group in the relevant, comprehensive health centre. After obtaining written consent from the participants to participate in the study, they will complete the questionnaires in the pre‐test phase. The person who will lead the sessions is a Ph.D. student in health education and health promotion.

Training sessions are taking place based on the priority of the educational domain (cognitive, emotional and behavioural). The first training sessions are based on the cognitive domain includes increasing comprehensibility and identifying GRASs, the next session based on the emotional domain includes increasing meaningfulness, and the last session based on the behavioural domain includes increasing manageability, respectively.

Since the qualitative phase of the study is conducted with a directed content analysis approach, the codes obtained from this phase are categorized as themes based on the components of ST. If these codes are common with the factors of the review phase of the study, the training content will be designed for this theme.

For other codes that are not included in these components of ST and form a new theme, if they are common with the factors obtained from the review phase of the study, the training content will be designed for the new theme.

The research team will try to finish all the training sessions before the 16th week of pregnancy and conduct the posttest in two phases (the first one immediately after the intervention and the second one during the third trimester of pregnancy [6 months after the intervention]). The participants will be asked to complete the questionnaires once again in the posttest and explain the delivery method and the reason for choosing it after childbirth. Until the end of the study, we will be in touch with the participants to the retention and follow‐up completely in the WhatsApp group.

#### Data collection

3.8.5

The measurement tools of this study are a demographics questionnaire, the Wijma Delivery Expectancy/Experience Questionnaire (W‐DEQ), Antonovsky's sense of coherence scale (SOC), and a choice of delivery method checklist. All these tools will be completed by participants themselves (self‐reporting). It is noteworthy that there would be changes in the measurement tools depending on the component obtained from the first and second phases of the study.

The W‐DEQ was developed by the Sweden Klaas Wijma in 1998 (Wijma, Wijma, & Zar, 1998). The W‐DEQ is a short, practical and common tool for evaluating FOC (Badaoui et al., 2019). This tool consists of 33 items that are scored based on a 6‐point Likert scale (from 0: very much to 5: not at all). The total score on this scale ranges between 0 and 165, and higher scores indicate higher levels of FOC. As the cut‐off point of this scale is 85, scores over 85, under 38, between 38 and 65 and between 66 and 84 represent clinical fear, mild fear, moderate fear and severe fear, respectively.

The 13‐item Antonovsky's sense of coherence scale (SOC‐13) measures comprehensibility (5 items), manageability (4 items) and meaningfulness (4 items) (Antonovsky, 1993). The items are scored based on a 7‐point Likert scale and the total score on this scale ranges between 13 and 91. A score within the ranges 13–60, 61–75 and 76–91 indicates low, moderate and high levels of SOC, respectively (Voogand et al., 2020).

#### Validity and reliability

3.8.6

Andaroon et al. (2020) and Mortazavi (2017) have localized and confirmed the validity and reliability of W‐DEQ in Iran (Mohamamdirizi et al., 2018; Mortazavi, 2017). The validity and reliability of Antonovsky's SOC‐13 have also been confirmed by Mohammadzadeh et al. (Mahammadzadeh, Poursharifi, & Alipour, 2010).

Considering the cultural features of the study area, the reliability of both tools will be assessed by the measurement of internal consistency using Cronbach's alpha and temporal stability measurement using the intraclass correlation coefficient (ICC).

#### Outcome variables

3.8.7

Reduced FOC and the selection of vaginal delivery are the primary outcomes and SOC is considered the secondary outcome of the training intervention in this study.

#### Sample size

3.8.8

Based on the Pukak formula and assuming a confidence coefficient of 95%, a test power of 80%, mean values (±*SD*) of 23 (±4.8) and 20 (±3.7) (related to “meaningfulness” in a similar study conducted based on ST [Tan et al., 2016]), and an attrition rate of 20%, the sample size for each group will be determined to be 38. A flow diagram of the randomized controlled protocol is shown in Fig. 2

$$n=\frac{{\left(Z_{1-\frac{\alpha }{2}}+Z_{1-\beta }\right)}^{2}\left(S_{1}^{2}+S_{2}^{2}\right)}{{\left({\bar{X}}_{1}-{\bar{X}}_{2}\right)}^{2}}$$

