#### Data analysis

3.8.9

After checking the normal distribution of data by the Kolmogorov–Smirnov test, the data will be statistically analysed in SPSS.

The participants' demographics and clinical information will be described by frequency distribution and percentage for qualitative data and mean and standard deviation for qualitative data.

The groups' pre‐ and post‐intervention mean scores of SOC and FOC will be compared by the independent sample *t* test and ANCOVA, respectively. In addition, analysis of variance with repeated measures based on the Greenhouse–Geisser test will be employed to compare the pre‐ and post‐intervention mean scores of SOC and FOC in each of the two groups.

The two groups will also be compared before and after the intervention using a chi‐square test to select the delivery method.

It is noteworthy that nonparametric tests will be used if the data are not normally distributed. The significance level in all tests will be 0.05. If there is missing data, the missing data will be handled using statistical methods.

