Target sample size	76
Recruitment status	Expected recruitment start date 23 Sep, 2022
Primary outcome(s)	Reduce fear of childbirth, Choice of natural childbirth
Key secondary outcomes	Sense of coherence

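### Thirty-eight women per group do not cover the stated 20% attrition: about 30 remain against the 32 to 33 the plan's own formula requires, so power is about 76–78%, not 80%

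*Protocol article*

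**What the plan says.** Section 3.8.8 of the protocol article gives a two-sample comparison-of-means formula and all of its inputs. The error rates are set by "assuming a confidence coefficient of 95%, a test power of 80" per cent, and the means and standard deviations are "of 23 (±4.8) and 20 (±3.7"), taken from the meaningfulness component in an earlier trial based on the same theory. The result is stated together with the allowance for loss: "and an attrition rate of 20%, the sample size for each group will be determined to be 38".

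Three other places bear on how to read 38:

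- Section 3.8.3 (Randomization) describes "two parallel groups of control and intervention using blocked randomization with blocks of 4 and 6", so allocation is taken as equal.
- Appendix A.1 lists "Target sample size" as 76, which is 2 × 38.
- Section 3.8.4 (Intervention) and Appendix A.1 plan training in four groups of six and two of seven, which is 24 + 14 = 38 women in the intervention arm.

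So 38 is the number enrolled per group, not the number expected to finish. The text does not say how the attrition allowance was applied.

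**The concern.** If 38 is the enrolled number and a fifth of those women are lost, the number left for analysis should be no smaller than the number the formula asks for. It is smaller. The 38 appears to come from adding 20% to the required number, which is not the same as allowing for a 20% loss from those enrolled.

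What is at stake is the accuracy of the power statement. The plan claims 80% power with 20% attrition, and its own figures do not deliver that even for the subscale it was sized on. The allowance is also likely to be needed. Women enter at 6 to 12 weeks' gestation and are followed until after childbirth (sections 3.8.1 and 3.8.4). Section 3.8.1 also lists irregular attendance, unreturned questionnaires, loss of contact and indications for caesarean section among the exclusion criteria, and several of these can arise only after enrolment.

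**Working it through.** **Inputs**, all from section 3.8.8 unless noted:

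- Two-sided alpha 0.05: the formula uses the normal quantile at 1 − α/2, and section 3.8.9 (Data analysis) says "The significance level in all tests will be 0.05".
- Power 0.80.
- Difference in means: 23 − 20 = 3.
- Sum of variances: 4.8² + 3.7² = 23.04 + 13.69 = 36.73.
- Attrition 20%; equal groups (section 3.8.3).

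**Step 1. Number needed for analysis.** n = (z₀.₉₇₅ + z₀.₈₀)² × (S₁² + S₂²) / (difference)².

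- Quantiles 1.96 and 0.84: 2.80² × 36.73 / 9 = 7.84 × 36.73 / 9 = 31.996, so 32.
- Exact quantiles (1.960 and 0.842): 7.849 × 36.73 / 9 = 32.03, so 33 if rounded up.

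**Step 2. Reproducing the stated 38.**

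- 32 × 1.2 = 38.4, rounded down to 38. This matches.
- A one-sided test does not explain it: n = 25.2, which becomes 30.3 when multiplied by 1.2 and 31.5 when divided by 0.8.

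**Step 3. Allowing for a 20% loss from those enrolled.** N = n / (1 − 0.20).

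| Completers needed | N per group | Total |
|---|---|---|
| 32 | 32 / 0.8 = 40 | 80 |
| 32.03 | 40.04, so 41 | 82 |
| 33 | 41.25, so 42 | 84 |

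**Step 4. What 38 leaves.**

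- After 20% loss: 38 × 0.80 = 30.4, or 30 whole women.
- Largest loss that leaves 32: 6/38 = 15.8%. Largest loss that leaves 33: 5/38 = 13.2%.
- The factor 1.2 by itself protects against a loss of 0.2/1.2 = 16.7%. Rounding 38.4 down to 38 lowers that further.

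**Step 5. Power with the women who remain.** At 30 per group the standard error is √(36.73/30) = 1.1065, and 3/1.1065 = 2.711. Normal-approximation power is Φ(2.711 − 1.960) = 77.4%. The same calculation at other sizes, with the noncentral t alongside:

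| Completers per group | Normal (plan's formula) | t test |
|---|---|---|
| 30 | 77.4% | 76.0% |
| 30.4 | 77.9% | 76.6% |
| 31 | 78.7% | 77.4% |
| 32 | 80.0% | 78.7% |
| 33 | 81.2% | 80.0% |

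**The case against.** The strongest reply accepts the slip and disputes its size. Four points deserve an answer.

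- **Rounding.** With conventional rounded quantiles the requirement is 32 and the corrected figure is 40, so the gap is two women per arm. The figures of 33, 42 and 84 come from an excess of 0.03 rounded up to a whole woman. This is fair: 40 per group is the plainest correction and 42 the upper end.
- **Choice of power figure.** Thirty completers is a loss of 8/38 = 21.1%. At exactly 20% loss the normal figure is 77.9%. The t-test figure also includes a change of method: by t test the formula's own 32 gives 78.7%, so only 78.7 − 76.0 = 2.7 points of the drop to 76.0% come from attrition. This also stands. The shortfall due to attrition is about 2 to 3 points.
- **Planned analysis.** Section 3.8.9 assigns ANCOVA to the post-intervention scores. If adjustment reduces the variance by a factor 1 − r², 30 completers recover 80% on the normal formula when 1 − r² = 30/32.03, that is r of about 0.25. Against the t-test requirement (30/33), r is about 0.30. Correlations of that size may well occur, but the plan states none and its formula takes no credit for adjustment. This could help the trial in practice; it does not make the printed sentence correct.
- **Relevance.** The calculation concerns a subscale of SOC, which section 3.8.7 (Outcome variables) makes the secondary outcome. Neither 80% nor 77% is the power for fear of childbirth or choice of vaginal delivery. This is true and a separate matter. It does limit what a corrected figure can be said to mean.

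Condensed reporting is no defence here. The formula, inputs and result are all printed, and they disagree.

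**Conclusion.** The concern holds. On the plan's own inputs, 38 enrolled per group does not give 80% power after 20% attrition. It leaves about 30 women against the 32 to 33 required. Power is 77.4–77.9% by the plan's formula, or 76.0–76.6% by t test. Keeping the stated power would need 40 to 42 per group, 80 to 84 in total rather than 76.

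The error is small: two to four women per group and roughly 2 to 4 points of power, the upper end of which includes the move from the normal to the t distribution. It should be corrected, but it does not by itself threaten the trial. The figures assume equal allocation, the same loss in both arms, an unadjusted comparison as in the printed formula, and the meaningfulness subscale as the outcome.

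**What to change.** Correct the statement in section 3.8.8 in one of two ways:

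- keep 38 per group and report about 77% power at 20% attrition; or
- keep 38 per group and 80% power, and state that this holds with attrition up to about 15%.

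In either case show the step as n / (1 − attrition), and say that the figure applies to an unadjusted comparison of the meaningfulness subscale, so that it is not read as the power for the primary outcomes. The cost is one sentence and a slightly less favourable figure, with no added participants.

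If the authors prefer to keep both 80% power and 20% attrition, the target becomes 40 to 42 per group. That is 4 to 8 more women in total, and the 76 in Appendix A.1 and the planned session group sizes would have to change to match.
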